### Mediator

#### Mediator

The amount of perceived control in a person’s life will be measured by the Pearlin Mastery Scale [27]. The scale consists of seven distinct items that are rated on a four-point scale. Higher scores indicate more perceived control; scores range from 7 to 35. The scale has good reliability [27].

### Moderators

#### Demographics

Demographic variables such as age, gender, parental nationality, family composition, family income and educational level will be screened for in a general questionnaire that measures user characteristics.

#### Alcohol use

The use of alcohol will be monitored using the four questions that make up the acronym CAGE: 'Cutting down, Annoyance by criticism, Guilty feeling, and Eye-openers’ [28]. The CAGE is a widely used concise screening tool for problematic alcohol consumption [29].

#### Personality

In order to measure the constructs neuroticism and conscientiousness, the NEO-Five Factor Inventory (NEO-FFI) will be administered [30]. Previous research has indicated that neuroticism often coincides with depression (for example, [31]). Those scoring higher on conscientiousness are expected to adhere better to the homework exercises and consequently benefit more from internet-based therapies. Only these two domains will be tested for to not exhaust participants more than necessary. A total of 12 questions on each of the domains will be answered on a 5-point Likert scale.

#### General expectancy

The Credibility/Expectancy Questionnaire of Devilly and Borkovec (CEQ) will be used to measure the expected change and credibility of proposed treatment [32]. It consists of six questions; four questions measure the 'thinking’ aspects about the treatment, two questions measure the 'feeling’ aspects of the questions. One question in both the 'feeling’ and 'thinking’ domain is rated from 0% to 100%; the remaining four questions are rated on a Likert-type scale from 1 to 9. Both factors have been found to have a high internal consistency and to have high test-retest reliability [32].

#### Expectancy with internet intervention

The 'Alles Onder Controle’ Expectancy Questionnaire (AOCEQ) has been designed for this research to ask what participants’ expectations are about the course. An open question investigates in which ways participants expect to gain benefits from this course. Three five-point Likert scale questions measure to which degree participants appreciate starting with the intervention immediately, that personalized feedback will be given in the internet group and to which degree they expect the course to help them feel less miserable.

#### General satisfaction with treatment

The satisfaction with the internet intervention will be measured by the Client Satisfactory Questionnaire-8 (CSQ-8), which consists of eight questions, each question is scored on a Likert-type scale from 1 to 4 [33]. The questionnaire addresses several elements that contribute to overall service satisfaction and is reported in a single dimension of overall satisfaction. A high internal consistency has been reported [33].

#### Satisfaction with the internet intervention

The 'Alles Onder Controle’ Satisfaction Questionnaire (AOCSQ) has been designed specifically to investigate to what degree participants are satisfied with this internet-based intervention. It includes questions on the number of sessions completed and, if applicable, the reasons for not finishing the course. The questionnaire further researches satisfaction with the separate elements of the intervention, such as the quality of the feedback, the clarity of the website and the appropriateness of the examples. Lastly, it explores whether participants were satisfied with the provided alternative to waiting, to which degree internet interventions are preferred over book interventions and to which degree feedback is preferred over non-feedback.

### Statistical analysis

The analyses will be conducted in agreement with the intention to treat (ITT) principle, as per the CONSORT statement [34]. Therefore missing endpoints will be imputed using state of the art imputation methods, as a reliable method for handling missing values [35]. Imputation allows for analyzing all participants in the condition to which they have been randomized, which contributes to guarantee the integrity of the randomization and restores loss of power due to dropout.

To answer the research questions we will first look at post-test differences between the two groups. We will use analysis of variance (ANOVA), with the baseline values and waiting time as covariates. Subgroup analyses will be performed for different characteristics. The difference in scores between the intervention group and the control group will also be expressed in effect sizes. We use Cohen’s *d* which is calculated by dividing the difference in mean scores of the two groups by their pooled standard deviation (Xexp-Xctrl/SDpooled). Effect sizes under 0.2 are considered to be small, those of 0.5 are moderate and effect sizes of 0.8 are considered to be large [36]. Furthermore, we will compare the rate of DSM-IV diagnosis of depression in both groups with logistic regression analysis. The clinical effects will also be calculated using reliable change [37]. The long-term outcomes will be analyzed with longitudinal analyses.

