### Sample size

The trial is powered to detect an effect size of d ≥0.40 [10,16] as statistically significant in a two-tailed test with α = 0.05 and power of (1 - β =) 0.80 with N = 99 per condition. To compensate for loss of follow-up of 20%, the trial requires starting with 99/0.8 = 124 participants per condition at baseline. The dropout rate of 20% is conservative, but from a power perspective a cautious approach. As this trial has two conditions, a total of N = 248 will be necessary for the complete trial.

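### Cohen's d is defined, on its plain reading, from unadjusted group means, while the test of the same difference adjusts for baseline

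*Protocol article*

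**What the plan says.** All the relevant text on the effect size is in the Statistical analysis section of the protocol article. The authors write that "we will first look at post-test differences between the two groups", using an analysis of variance "with the baseline values and waiting time as covariates", which is an analysis of covariance. The same paragraph adds that the group difference will be expressed as an effect size as well. Cohen's d is obtained by "dividing the difference in mean scores of the two groups by their pooled standard deviation", and a bracketed formula repeats this with the two group means and the pooled SD. Nothing in the formula refers to the model or its covariates. The words raw, observed and adjusted do not appear.

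The design is stated on the same scale. Under Sample size, "The trial is powered to detect an effect size of d ≥0.40", with "power of (1 - β =) 0.80 with N = 99 per condition". The Assessments section places the baseline measurement, which includes the CES-D, before randomisation.

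**The concern.** The test and the effect size describe the same contrast but, read plainly, rest on different estimates. The test removes the part of the post-test difference that baseline score predicts. A d built from observed means keeps it. If one arm happens to start with a higher mean CES-D, some of that gap persists at post-test and enters d. The p-value beside it comes from a model that has taken the gap out.

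What is at stake is the accuracy of the reported magnitude. The article also interprets d against conventional thresholds (0.2, 0.5 and 0.8), so a shift of a tenth or more can change how the result is described. A more precise estimate on the same scale is available from the model already planned.

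**Working it through.** **1. The plan's own figure.** Inputs from Sample size: d = 0.40, two-sided α = 0.05, power 0.80.

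n per arm = 2 × (1.960 + 0.842)² / 0.40² = 2 × 7.85 / 0.16 = 98.1, rounded up to 99. Power at 99 per arm is 0.804 by the normal approximation and 0.800 by the noncentral t. Allowing for 20% loss, 99 / 0.8 = 123.75, rounded up to 124 per arm, or 248 in total. The stated figures reproduce exactly.

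**2. Input not in the article.** The correlation r between baseline and post-test CES-D is not given. I assume 0.3 to 0.7, with 0.5 as the middle value. Waiting time, the other covariate, is not modelled here.

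**3. Formulas**, in SD units with n per arm:
- SE of raw d ≈ √(2/n). The SD of a chance baseline imbalance is the same quantity.
- SE of d with an adjusted numerator and the same pooled-SD denominator ≈ √(2/n) × √(1 − r²).
- Raw d minus adjusted d ≈ r × baseline imbalance, so its SD is r × √(2/n), and 95% of trials lie within ±1.96 times that.

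**4. Results at 99 per arm**, where √(2/99) = 0.142:

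| r | SE raw d | SE adjusted d | Variance reduction (r²) | SD of raw − adjusted | 95% limit of the difference |
|---|---|---|---|---|---|
| 0.3 | 0.142 | 0.136 | 9% | 0.043 | 0.084 |
| 0.5 | 0.142 | 0.123 | 25% | 0.071 | 0.139 |
| 0.7 | 0.142 | 0.102 | 49% | 0.099 | 0.195 |

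The 95% half-width of d falls from 0.279 to 0.266, 0.241 or 0.199. A baseline gap of 0.2 SD would move raw d by 0.2 × r, that is 0.06, 0.10 or 0.14.

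**5. Results at 124 per arm**, where √(2/124) = 0.127. This case is relevant because the article plans to impute missing endpoints and analyse everyone randomised. The SE falls from 0.127 to 0.121, 0.110 or 0.091, and the 95% limits of the difference are 0.075, 0.124 and 0.174.

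**6. Simulation check** (10,000 trials for each r, 99 per arm, true d = 0.40). Mean raw d was 0.404, 0.403 and 0.402. Mean adjusted d was 0.404, 0.401 and 0.401. Both are centred on the truth, so raw d is noisier but not biased. The SDs were 0.145 against 0.139, 0.145 against 0.127, and 0.146 against 0.105. The SD of the difference was 0.044, 0.071 and 0.100, in line with the formulas.

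**The case against.** The strongest reply is that the text never calls the means unadjusted. Model-adjusted means over a pooled SD would also fit the words, and a condensed article may leave such detail to an analysis plan. The first half stands: raw means are an inference, although unqualified group means over their pooled SD are the textbook unadjusted d. The second half has less force. The article does not leave d open; it prints a formula, and that formula has no link to the model described just before it. If adjusted means were intended, the same clarifying sentence is needed, because two analysts could follow this text and report different values.

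A second reply is that an adjusted test with a conventional descriptive d beside it is a coherent plan. That also stands. There is no contradiction, only precision given up without need.

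Three stronger readings are tempting, and the article supports none of them:
- **That d is the main result.** The text presents d as an additional expression of the difference. It uses 0.40 only to set the sample size, and no success rule compares the observed d with it.
- **That d and the primary test may give conflicting significance verdicts.** That would need an unadjusted significance test, and none is planned.
- **That raw d is biased.** Over randomisations it is not, as the simulation shows.

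Finally, the size rests on an assumed r. At r = 0.3 the gain in standard error is slight. Even at r = 0.5 the 95% limit is not the usual case: with an SD of 0.071, the mean absolute shift is about 0.071 × 0.80 = 0.06.

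**Conclusion.** The point holds as a minor one. On its plain reading, the article reports an effect size that carries chance baseline imbalance and is less precise than the adjusted estimate from the model it already plans to fit. The direction is certain for any non-zero r; the amount is not. Over the assumed range of r the loss runs from slight to material. At r = 0.5 the 95% limit of the difference between the two versions is about a third of the planning effect with 99 per arm (0.139 / 0.40 = 0.35), and a little less if all 124 are analysed (0.124 / 0.40 = 0.31). The conclusion rests on three assumptions: observed means are intended, r lies between 0.3 and 0.7, and waiting time can be ignored in the calculation. The primary test and the trial's conclusion on effectiveness do not depend on this point.

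**What to change.** Add one sentence to the Statistical analysis section: the numerator of Cohen's d is the covariate-adjusted mean difference from the primary model, the denominator is the pooled SD of the unadjusted scores, and d is given with its 95% confidence interval; d from observed means is reported as a supplement. Keeping the unadjusted SD in the denominator matters, because dividing by the model's residual SD would inflate d and break comparison with 0.40 and the conventional thresholds. The change needs no new data, no further model and no change to the sample size.

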### Inclusion and exclusion criteria

Eligible participants are adults, aged 18 or over, registering for regular treatment at one of the participating MHCs who meet the criteria for a *Diagnostic and Statistical Manual of Mental Disorders*, fourth edition (DSM-IV) diagnosis of major depression as measured with the Clinical International Diagnostic Interview (CIDI) by a trained research assistant, have access to the internet, and adequate proficiency in Dutch. Exclusion criteria are starting or changing type of dosage of antidepressant medication, the presence of a bipolar or psychotic disorder, and an increased risk of suicide. Comorbid disorders other than bipolar or psychotic disorders are allowed.

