### Secondary outcomes

#### Diagnosis of depression

The CIDI will be used to assess whether the DSM-IV diagnosis of depression has been met. The CIDI has been developed by the World Health Organization to assess DSM-IV Axis-I diagnoses [20]. For the purposes of this study, only section E will be administered, which allows for screening for depressive disorders. The CIDI will be conducted by phone by a trained interviewer.

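### The logistic model for post-test diagnosis names no covariate and its own baseline is constant by eligibility; adjusting for baseline CES-D would gain precision without new data

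*Protocol article*

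**What the plan says.** Entry requires a DSM-IV "diagnosis of major depression as measured with the Clinical International Diagnostic Interview (CIDI) by a trained research assistant" (Inclusion and exclusion criteria). The same interview supplies a secondary outcome: "The CIDI will be used to assess whether the DSM-IV diagnosis of depression has been met" (Diagnosis of depression). Table 1 schedules the CIDI at baseline and post-test only, and the CES-D at baseline and at all three later assessments.

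Under Statistical analysis, the post-test comparison is specified as follows: "We will use analysis of variance (ANOVA), with the baseline values and waiting time as covariates". Later in the same paragraph, for the diagnosis outcome, "we will compare the rate of DSM-IV diagnosis of depression in both groups with logistic regression analysis". No covariate is named for the logistic model. The next sentence adds a reliable-change calculation without naming a scale.

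**The concern.** The section has one rule for using baseline information, and that rule was written for continuous scores. For the CES-D it works: the baseline score varies between patients and explains part of the post-test score. For the diagnosis it cannot work, because eligibility makes the baseline diagnosis positive for every patient. A constant covariate adjusts for nothing.

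Patients who all meet the diagnosis at entry still differ in severity, and the more severe can be expected to meet it again 6 to 8 weeks later more often. If the model holds only the treatment term, or treatment and waiting time, that variation stays unexplained and the test has less power than the collected data allow. What is at stake is precision on a secondary outcome, not bias in the comparison.

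**Working it through.** **1. The plan's own sample-size figures.** Inputs from the Sample size section: "The trial is powered to detect an effect size of d ≥0.40", "in a two-tailed test with α = 0.05", power "0.80 with N = 99 per condition".

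- n per arm = 2(1.960 + 0.842)² / 0.40² = 2 × 7.851 / 0.16 = 98.1, rounded up to 99.
- Dropout of 20%: 99 / 0.8 = 123.75, rounded up to 124, as stated ("the trial requires starting with 99/0.8 = 124 participants per condition at baseline").
- Total: 2 × 124 = 248.

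All three figures reproduce. They rest on a standardised mean difference, so the trial was not sized on the diagnosis outcome. The 99 per arm is used below as the number observed.

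**2. What each possible covariate contributes to the diagnosis model.**

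| Baseline quantity | Collected at baseline? | Varies between enrolled patients? | Named for the logistic model? |
|---|---|---|---|
| CIDI diagnosis | Yes | No, positive for all by eligibility | No |
| CES-D score | Yes (Table 1) | Yes | No |
| Waiting time | Not a questionnaire item | Yes, variable by location and over time | No (named for the ANOVA) |

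So the one baseline severity measure that could help is available, and the article's covariate rule does not reach it.

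**3. What adjustment could gain.** The article gives no CIDI reliability, no expected diagnosis rates and no correlation between CES-D and CIDI, so everything in this step is assumed. In the simulation, true severity is standard normal and the CIDI reads it with reliability 0.7 or 0.8. The cut-off makes 70% of interviewed patients positive, and the positives are enrolled. All improve by 0.6 SD on average and the intervention adds 0.4 SD. The SD of individual true change is 0.5, 0.8 or 1.2. There are 198 patients and 1,500 replicates per cell. In the cases of main interest the post-test diagnosis rates are about 61% to 65% against 50% to 51%, and the CES-D baseline-to-post-test correlation is 0.45 to 0.67.

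| CIDI reliability | SD of true change | Power, unadjusted | Power, adjusted for baseline CES-D | Gain (points) |
|---|---|---|---|---|
| 0.7 | 0.5 | 0.51 | 0.61 | 10 |
| 0.7 | 0.8 | 0.40 | 0.47 | 7 |
| 0.7 | 1.2 | 0.29 | 0.31 | 2 |
| 0.8 | 0.5 | 0.62 | 0.72 | 10 |
| 0.8 | 0.8 | 0.45 | 0.52 | 7 |
| 0.8 | 1.2 | 0.30 | 0.34 | 4 |

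The Monte Carlo standard error of one power figure is at most √(0.5 × 0.5 / 1500) = 0.013. Under no treatment effect the rejection rates were 0.042 unadjusted against 0.040 adjusted, and 0.051 against 0.051.

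This set-up is favourable to adjustment if CES-D and CIDI measure one shared severity. A further simulation gave gains of about 5 to 12 points when CES-D tracks the CIDI severity closely, and about 0 to 5 when it does so imperfectly. In that simulation, too, the type I error stayed near 0.05. The defensible range is therefore about 0 to 12 points.

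**The case against.** The best counter-argument is that the article is silent rather than wrong. It names logistic regression without saying that the model has no covariates, and a condensed article commonly leaves such lists to the analysis plan. This stands in part: the text does not show that the model will be unadjusted. What remains is that the section does state a covariate rule, and that its baseline part cannot serve the one binary outcome it names.

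Four stronger readings are tempting, and the documents do not support them.

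- *No usable baseline covariate exists.* Baseline CES-D is collected from all patients; only the baseline diagnosis is uninformative.
- *Patients who lose the diagnosis will be called recovered through measurement noise.* The plan is a randomised comparison of rates between arms and nowhere labels loss of diagnosis as recovery. Noise common to both arms does not create a difference.
- *Absolute remission rates will be overstated.* This holds only if few patients truly improve. With assumed sensitivity and specificity of 0.80, true remission of 40% is observed as 0.4 × 0.8 + 0.6 × 0.2 = 44%. True remission of 60% is observed as 0.6 × 0.8 + 0.4 × 0.2 = 56%, and at 50% the errors cancel.
- *The outcome needs a minimum change or a combined CIDI and CES-D definition.* Reliable change is already planned separately, post-test diagnostic status is a conventional outcome, and a composite would be a choice of a different endpoint.

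One caveat applies to any version of the analysis. Outcome assessors are not blinded (Randomization and blinding), so equal interview error in both arms is an assumption. Covariate adjustment does not address that.

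**Conclusion.** The point holds as a modest, low-cost improvement. The logistic comparison of post-test diagnosis has no stated covariate, its own baseline is constant by eligibility, and an informative baseline measure that every patient provides is not brought in. The between-arm test is valid with or without adjustment, provided interview error does not differ by arm.

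The gain is about 0 to 12 points of power at 99 per arm. It is near zero if baseline CES-D predicts post-test diagnosis weakly or individual change is very variable, and near the top only if CES-D closely tracks the severity behind the CIDI. None of the inputs that decide this are in the article. The outcome is secondary; the baseline-adjusted CES-D analysis and the figures of 99, 124 and 248 are untouched.

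**What to change.** In Statistical analysis, replace the sentence on the diagnosis rate with wording such as: *The rate of DSM-IV diagnosis at post-test will be compared between arms by logistic regression adjusted for baseline CES-D score and waiting time; a standardised (marginal) risk difference with its confidence interval will be reported alongside the conditional odds ratio.* If the full analysis plan already says this, no change is needed beyond making the two texts agree.

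The cost is one sentence and no new data. The adjusted odds ratio is conditional on the covariates and is not directly comparable with an unadjusted one, which is why the marginal risk difference should be reported with it.

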### Economic outcomes

The economic evaluation will be conducted from a societal perspective, therefore it will include not only the intervention costs and costs stemming from healthcare uptake (direct medical costs), but also the patients' out of pocket costs (direct non-medical costs) and costs stemming from productivity losses due to absenteeism and work cutback days (indirect non-medical costs). Costs will be based on the Dutch standard cost prices [24] and productivity losses will be valued using the friction costs method, as per the Dutch guideline for economic evaluation. Quality-adjusted life years (QALYs) will be calculated on the basis of the EQ-5D. Having calculated the costs and QALYs allows for a cost-utility analysis, which can be used to compare this intervention’s gains against those of other interventions for depressive disorders. A cost-effectiveness analysis can be carried out by dividing the difference in costs by the difference in effect, as is customary in the field of mental health. Bootstrapping will be used to ascertain the amount of uncertainty surrounding the incremental cost effectiveness ratio (ICER) estimates and graphically depicted on the ICER plane and in the acceptability curve.

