#### Quality of life

The EuroQol 5-Dimensions questionnaire (EQ-5D), which consists of five items, will be used to measure quality of life. It registers the level of perceived problems (no, some or extreme) in five domains (mobility, self-care, usual activities, pain/discomfort and anxiety/depression). A total of 486 distinct health states can be scored which are located between 0, which indicates worst health possible, and 1, which indicates perfect health [23].

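### The EQ-5D description is wrong on its own inputs (243 states, not 486) and is not anchored as a QALY scale; the economic comparison also states no baseline adjustment

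*Protocol article*

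**What the plan says.** **The instrument.** The Quality of life section (Secondary outcomes) states: "The EuroQol 5-Dimensions questionnaire (EQ-5D), which consists of five items, will be used to measure quality of life". It continues: "It registers the level of perceived problems (no, some or extreme) in five domains". It then says: "A total of 486 distinct health states can be scored which are located between 0, which indicates worst health possible, and 1"; the upper end stands for perfect health.

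**Its use.** The Economic outcomes section states: "Quality-adjusted life years (QALYs) will be calculated on the basis of the EQ-5D". It intends the resulting cost-utility analysis to allow comparison with other interventions for depression. The next step, the cost-effectiveness analysis, is described as "dividing the difference in costs by the difference in effect, as is customary in the field of mental health". On uncertainty: "Bootstrapping will be used to ascertain the amount of uncertainty surrounding the incremental cost effectiveness ratio (ICER) estimates". The section names neither a value set nor any covariate.

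**The clinical comparison.** The Statistical analysis section does name covariates for the post-test comparison: "We will use analysis of variance (ANOVA), with the baseline values and waiting time as covariates".

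**Data available.** Table 1 marks EQ-5D and TiC-P at T0, T1, T2 and T3. The section on costs from a societal perspective says that the baseline TiC-P looks back over the 4 weeks before the intervention.

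**The concern.** There are two separate matters.

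**The EQ-5D text.** The number of states does not follow from the items and levels given two sentences earlier. More important is the anchor. QALYs are comparable across interventions only when 0 stands for dead and 1 for full health. A scale that puts 0 at the worst describable health agrees with this only if that state happens to be valued exactly at 0. If the value set in use places some states below dead, an analyst who follows the text would either rescale all utilities or floor the negative ones. Rescaling changes the unit of the QALY. Flooring compresses differences among the most ill patients. Either would undermine the cross-intervention comparison that the economic section is meant to support.

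**Baseline adjustment.** Baseline utility is itself a term in the area under the utility curve, and it also predicts later utility. A chance difference between arms at T0 therefore passes into incremental QALYs unless it is adjusted for. Baseline costs work differently. They cover a period before the intervention and are not part of follow-up costs, so they matter only as a predictor. At stake is avoidable noise in the ICER, its bootstrap cloud and the acceptability curve.

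**Working it through.** **1. Number of states.** Inputs from the Quality of life section: 5 items, 3 levels each.

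- States = levels^items = 3^5 = 243.
- Stated figure: 486 = 2 × 243. It does not reproduce.
- The count appears in no later formula, so it does not affect QALYs or the ICER.

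**2. Anchor, if applied literally by rescaling.** Let w be the utility of the worst state on the dead-to-full-health scale. The document does not give w, so it is assumed here. Rescaling to worst = 0 gives u' = (u - w)/(1 - w). A QALY difference is then multiplied by 1/(1 - w), and an ICER by (1 - w).

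| w (assumed) | QALY difference × | ICER × |
|---|---|---|
| 0 | 1.00 | 1.00 |
| -0.1 | 0.91 | 1.10 |
| -0.33 | 0.75 | 1.33 |
| -0.6 | 0.63 | 1.60 |

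The effect of flooring negatives at 0 depends on how many patients are in such states and cannot be computed from the document.

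**3. Precision gain for QALYs.** The assumptions are trapezoidal QALYs at 0, 8, 26 and 52 weeks, the same utility SD at each visit, and an equal correlation r between all visits. The visit times follow Table 1 (8 weeks, 6 months, 12 months). The trapezoid rule, the SD and r are not in the document.

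- Weights: 4/52, 13/52, 22/52 and 13/52 = 0.077, 0.250, 0.423 and 0.250.
- Sum of squared weights: 0.0059 + 0.0625 + 0.1790 + 0.0625 = 0.310.
- Slope of QALY on baseline: b = 0.077 + 0.923r.
- Variance of QALY in units of SD²: V = r + (1 - r) × 0.310.
- Share of variance removed by adjustment: b²/V.

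| r | b | V | b²/V | SE ratio √(1 - b²/V) |
|---|---|---|---|---|
| 0.3 | 0.35 | 0.517 | 24% | 0.87 |
| 0.5 | 0.54 | 0.655 | 44% | 0.75 |
| 0.7 | 0.72 | 0.793 | 66% | 0.58 |

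The percentages depend on neither the SD nor the sample size. To give them a scale, assume SD 0.25 and r = 0.5, with SE = √(2 × 0.25² × V/n).

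- With 99 per arm (the Sample size section's figure after dropout): SE = 0.029 unadjusted and 0.021 adjusted.
- With 124 per arm (all randomized, as the planned imputation implies): 0.026 and 0.019.

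**4. Chance imbalance is the same quantity.** With 99 per arm, one SE of the baseline difference is 0.25 × √(2/99) = 0.036. It shifts the unadjusted QALY difference by 0.036 × 0.54 = 0.019. Then 0.019² + 0.021² ≈ 0.029². The shift is the variance component that adjustment removes, not an additional harm.

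**5. A simpler check.** If 0.3, 0.5 or 0.7 is instead taken directly as the correlation between baseline and the whole QALY, the SE ratio √(1 - r²) is 0.95, 0.87 or 0.71. The two results are consistent. Between-visit correlations of 0.3, 0.5 and 0.7 imply baseline-to-QALY correlations of √0.24 = 0.49, √0.44 = 0.67 and √0.66 = 0.81.

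**6. Costs.** No correlation between baseline and follow-up costs is given, and none can be inferred, so no figure is offered.

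**The case against.** The strongest objection is that the article does not say the economic differences are raw. A ratio of two differences is simply what an ICER is, and it holds equally for regression-adjusted differences. The sentence on that ratio also concerns the cost-effectiveness analysis, while the QALY analysis is introduced just before it. Covariates for an economic model are often left to a fuller document. A reader might infer that the plan commits to an unadjusted comparison, or that the ICER will be biased. Neither is supported. The text is silent on adjustment, and under randomization an unadjusted comparison is imprecise but not systematically wrong. An unadjusted bootstrap would already show the added uncertainty.

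A reader might also infer that the ICER will be mis-scaled. The document does not show that either. Nowhere does it say that utilities will be rescaled or that negative values will be floored. The Quality of life text may be only a loose description of a published scoring.

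Finally, the size of the precision gain rests on assumed correlations, and it would be wrong to treat baseline costs as feeding into follow-up costs in the way that baseline utility feeds into QALYs. Follow-up costs also include session counts reported by the mental health centers.

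All of this stands and limits the point. It does not remove the wrong state count, the anchor that conflicts with the stated use, or the contrast between a clinical analysis with named covariates and an economic one with none.

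**Conclusion.** The EQ-5D description is in error. The document's own inputs give 243 states, not 486, and its 0-to-1 scale, read literally, is not one from which comparable QALYs can be calculated. The count has no numerical consequence. The anchor has one only if it is applied as written and some states are valued below dead. The ICER factor under rescaling is then 1.1 to 1.6 for an assumed worst-state utility of -0.1 to -0.6. Because no value set is named, nothing else in the document corrects the description.

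The absence of stated baseline adjustment is a lesser matter: a missed gain in precision, with chance imbalance left in. Adjustment would cut the variance of the QALY difference by about 24% to 66% for assumed between-visit correlations of 0.3 to 0.7, equal across visits, with trapezoidal QALYs. The gain for costs is unknown.

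**What to change.** **Text.** In the Quality of life section, change the count to 243. State that utilities come from a named value set with 0 = dead and 1 = full health, and that any negative values are kept. Name the same value set in the Economic outcomes section.

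**Analysis.** State that within each bootstrap sample incremental QALYs are estimated by regression on arm and baseline EQ-5D utility, and incremental costs by regression on arm and baseline TiC-P costs. The ICER, the cost-effectiveness plane and the acceptability curve are then built from these adjusted differences. Location, as the randomization stratum, may be added to both models. Resampling within arm is optional.

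**Cost.** A text correction and two regression lines in the bootstrap code. No new data are needed, since both baseline measures are already collected, and recruitment is still ongoing, so the change can be fixed before analysis.
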